### Power calculation/sample size

Sample size was calculated taking into account the design effect (due to group randomization) and the expected effect size. The measures with the highest expected effect size within the duration of the study of 20 months are: empowerment (0.38) and hope (0.50) [26, 43]. Cohen’s d was used as the measure for effect size with *α* = 0.05 and a power of 0.80, based on a two-sided test. The design effect used is estimated to be 1.5 based on an average cluster size of 38 and an intra-cluster correlation (ICC) of 0.013. Based on the effect size of empowerment (0.38; the lowest of the two above mentioned) a sample of 128 clients per condition is needed. When taking into account a reduction of 20 % for loss due to follow up, 160 clients per group will be recruited to achieve the required power. To reach a sufficient amount of clients 16 teams will be included in the study, which together provide services to 890 clients.

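### The 128 clients per condition do not give the stated two-sided 80% power: the stated inputs need about 163, and 128 gives about 70%

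*Protocol article*

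**What the plan says.** The section on power and sample size in the protocol article sets out one complete calculation. It uses Cohen's d, alpha 0.05 and "a power of 0.80, based on a two-sided test". On clustering it says: "The design effect used is estimated to be 1.5", derived from an average cluster size of 38 and an intra-cluster correlation of 0.013. Two candidate effect sizes are named, 0.38 for empowerment and 0.50 for hope, and the smaller is used: "Based on the effect size of empowerment (0.38; the lowest of the two above mentioned) a sample of 128 clients per condition is needed". After an allowance of 20% for loss to follow-up, "160 clients per group will be recruited to achieve the required power". Sixteen teams, serving 890 clients between them, are to supply these participants. The study design section says that teams are allocated equally to the two arms.

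The paragraph mentions no one-sided test, no variance reduction from baseline or repeated measurements, and no other cluster size.

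**The concern.** Every input to a standard comparison of two means is printed, so the result can be checked without outside information. Run two-sided, as stated, the calculation gives a clearly larger number than 128. Run one-sided at 0.05, it gives 128 and 160 almost exactly.

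At stake is the only stated justification for the trial's size. If 128 analysed clients per condition deliver less than 0.80, a non-significant result on the outcome used for planning would be credited with more evidential weight than it has. The article presents this as the first controlled effect study of the CARe methodology, so an inconclusive result could easily be over-read.

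**Working it through.** **Inputs**, all from the power and sample-size section except the allocation: d = 0.38 (so SD = 1); alpha = 0.05, two-sided; power 0.80; design effect (DE) 1.5; loss 20%; equal allocation (study design section).

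**Design effect.** 1 + (38 − 1) × 0.013 = 1.481, which the article rounds to 1.5. This step is sound.

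**Formula.** n per condition = 2 × (z_alpha + z_power)² / d² × DE, with z_power = 0.842. The number to recruit is n / (1 − 0.20). Results below use unrounded z values.

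**Reproducing the article's figure (one-sided alpha 0.05, z = 1.645)**
- 2 × (1.645 + 0.842)² / 0.38² = 85.6
- 85.6 × 1.5 = 128.4
- 128.4 / 0.8 = 160.6

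These match the printed 128 and 160. The step from 128 to 160 is itself correct: 128 / 0.8 = 160.

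**The calculation as described (two-sided alpha 0.05, z = 1.960)**
- 2 × (1.960 + 0.842)² / 0.38² = 108.7
- 108.7 × 1.5 = 163.1
- 163.1 / 0.8 = 203.8, so about 204 to recruit

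Small variants do not close the gap. The unrounded DE of 1.481 gives 161. A t-based calculation at DE 1.5 gives 164.5 to 165, or up to 207 recruited. The stated 128 is 35 analysed clients per condition short of 163, about 21% lower. The stated 160 is 44 short of 204.

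**Power that 128 analysed per condition provides**
- Effective n per condition: 128 / 1.5 = 85.3
- Standardised effect: 0.38 × √(85.3 / 2) = 2.482
- Two-sided power: Φ(2.482 − 1.960) = Φ(0.522) = 0.699
- One-sided power: Φ(2.482 − 1.645) = Φ(0.837) = 0.799

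With DE 1.481 the two-sided figure is 0.705. Even if all 160 per group were analysed with no loss, two-sided power at DE 1.5 would be 0.793.

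**What else could give 128 with a two-sided test?** One input would have to differ from the text: d of about 0.43, or DE of about 1.18, or an adjustment for a baseline correlation of about 0.46, since 163.1 × (1 − 0.464²) = 128. The paragraph states none of these.

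**Sensitivity, on assumptions that are not the article's**
- *Smaller clusters.* The target of 320 clients over 16 teams implies 20 per team, or 16 after loss, in place of 38. Then DE is 1 + 19 × 0.013 = 1.247 or 1 + 15 × 0.013 = 1.195, and two-sided power at 128 is 0.78 or 0.79.
- *Few teams.* A test on 14 team-level degrees of freedom (16 − 2) gives 0.64 at DE 1.5, and 0.72 to 0.73 at the two smaller design effects.

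None of these reaches 0.80.

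**The case against.** The strongest objection is that the cause is inferred. The article says two-sided and shows no working. The one-sided route gives 128.4, which would usually be rounded up to 129. A two-sided calculation with a baseline correlation of about 0.46 also arrives at 128, and the analysis section does plan a longitudinal model using baseline, 10-month and 20-month data. This part stands: a one-sided calculation is the simplest explanation, not a proven one. It does not rescue the figure, because the sample-size paragraph claims no such allowance and 128 still does not follow from the inputs given.

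Second, the smaller-cluster and 14-degree-of-freedom figures are not the article's. It states a cluster size of 38 and, in the section reviewed, fixes no degrees-of-freedom rule for the mixed model; with so small an intra-cluster correlation, 14 may be too strict. That is fair. They are sensitivity checks, and the finding rests on 163 against 128 and 0.70 against 0.80.

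Third, the impact has limits. The calculation concerns empowerment, a secondary outcome; no power is stated for recovery, social functioning or quality of life. The over-reading of a null result therefore applies directly to empowerment only. All clients of the 16 teams are invited, and recruiting 408 (2 × 204) of 890 would take 46% participation against 36% for 320, so enrolment might exceed the target. The article nonetheless commits only to 160 per group and ties the required power to that number.

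**Conclusion.** The concern holds. On the article's own inputs, a two-sided test at alpha 0.05 with power 0.80 needs about 163 analysed and 204 recruited per condition, not 128 and 160. With 128 analysed per condition, two-sided power is about 0.70, ten percentage points below the stated value.

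This rests on d = 0.38, DE 1.5, equal arms, an unadjusted alpha of 0.05 and the normal approximation. Using the t-based method or the unrounded design effect changes the requirement only within 161 to 165 and the power only within 0.69 to 0.71. The printed numbers are consistent with a one-sided alpha of 0.05; that is the likely origin, and the conclusion does not depend on it.

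As a separate matter, the analysis section applies a Bonferroni adjustment across the four secondary outcomes, which include empowerment. At 0.05 / 4 = 0.0125, power with 128 per condition at DE 1.5 would be about 0.49. So 0.70 is not a pessimistic figure.

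**What to change.** Correct the sample-size paragraph in one of two ways.

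- Keep the two-sided test and power of 0.80, and report the requirement that follows: about 163 analysed and 204 recruited per condition at a design effect of 1.5.
- Keep 128 analysed and 160 recruited per condition, and restate the two-sided power as about 0.70 at a design effect of 1.5.

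If the calculation in fact used a further input, such as a baseline correlation or a smaller cluster size, the paragraph should state that input and its value and give the power that results. On cluster size alone, the clients per team implied by the recruitment target give 0.78 to 0.79 by normal approximation, or 0.72 to 0.73 on 14 degrees of freedom, so 0.80 would still not be met.

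The cost is one rewritten paragraph and a less favourable power statement. The design and analysis do not change, and further enrolment is needed only if 0.80 is to be kept as the target.

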### Statistical analysis

Data will be analysed according to intention-to-treat, meaning that participants will be analysed in the group to which they were allocated by randomization [65]. SPSS 19 will be used for the analysis. Because the study has a cluster randomized design, longitudinal multilevel analysis (linear mixed modeling with random intercepts at both team level and individual level) is the analysis method of choice. First, effectiveness of the CARe Methodology on the three primary outcomes, recovery, social functioning and quality of life, will be evaluated. Subsequently, the effectiveness on four secondary outcomes, hope, empowerment, self-efficacy beliefs and need for care will be evaluated. An alpha correction (i.e., Bonferroni adjustment) will be applied across analysis of the primary measures in order to maintain a family-wise alpha level of 0.05. A separate Bonferroni adjustment will be applied to the set of analysis for the secondary measures to maintain their family-wise alpha level at 0.05. Furthermore, in separate analyses we will assess whether different types of predictors explain the outcomes: (1) client characteristics (age, gender, having a partner, type of housing, diagnosis), (2) symptom severity (BSI), (3) health and day care utilization. Only predictors that influence the prediction of the outcome measures will be added tot the final model. Outcomes will be measured at 10 months and 20 months post-baseline (time will be analyzed as a categorical variable).

To detect significant differences in the baseline characteristics between the intervention group and control group descriptive analysis will be used. When necessary these differences will be taken into account in the analysis. Missing data and drop-outs will be analysed and accounted for by multiple imputation if the assumption of data missing at random (MAR) is not violated [66].

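### The stated 0.80 power does not follow from 128 clients per arm in 16 teams: on the plan's own two-sided inputs it is about 0.70, and about 0.64 once the small number of teams is allowed for

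*Protocol article*

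**What the plan says.** Protocol article, Power calculation/sample size:

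- The effect is expressed as Cohen's d and tested at alpha 0.05; the section claims "a power of 0.80, based on a two-sided test", which is the claim examined here.
- On clustering, the section gives this: "The design effect used is estimated to be 1.5 based on an average cluster size of 38 and an intra-cluster correlation (ICC) of 0.013".
- The governing effect: "Based on the effect size of empowerment (0.38; the lowest of the two above mentioned"). From this the section derives 128 clients per condition, or 160 recruited after 20 % loss.
- The team count comes last, as the way to find enough clients: "16 teams will be included in the study".

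Protocol article, Study design: teams are the unit of randomization, stratified by organisation (three of them), with equal allocation to the arms.

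Protocol article, Statistical analysis: the model is "linear mixed modeling with random intercepts at both team level and individual level". Separate Bonferroni adjustments apply to the three primary and the four secondary outcomes.

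**The concern.** The section presents a finished calculation with a definite result, so the result can be checked. Two things look wrong with it.

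First, 128 per condition is too small for the inputs listed beside it if the test is two-sided, as stated.

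Second, the number of teams plays no part in the power. A design effect enlarges the variance of the arm difference to reflect clustering. It does not reflect that this variance must be estimated from few teams. With 8 teams against 8 and a random team intercept, the arm effect is judged against between-team variation on roughly 14 df. The two-sided 5 % critical value is then 2.14 rather than 1.96.

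At stake is how a null result will be read. A reader told that power was 0.80 will take a non-significant finding as stronger evidence against an effect of d = 0.38 than the design supports. Correcting only the sidedness, or only the cluster size, would still leave a printed power that 16 teams do not give on this calculation.

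**Working it through.** **Inputs from the protocol.** d = 0.38; two-sided alpha 0.05; power 0.80; design effect (DE) 1.5 from cluster size 38 and ICC 0.013; 128 analysed and 160 recruited per arm; 16 teams; equal allocation; three strata.

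**Assumptions.** 8 teams per arm, equal team sizes, and one post-baseline comparison without baseline adjustment. The protocol prints no formula, so the method is inferred from which calculation returns 128.

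**1. Reproducing 128.** Design effect: 1 + (38 − 1) × 0.013 = 1.481, rounded to 1.5. Individual-level n per arm = 2(z_alpha + z_power)² / d².

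- Two-sided: 2(1.960 + 0.842)² / 0.38² = 108.7; × 1.5 = 163 (161 with DE 1.481). This is not 128.
- One-sided: 2(1.645 + 0.842)² / 0.38² = 85.6; × 1.5 = 128.4. This reproduces 128.
- Attrition: 128 / 0.8 = 160, as stated. From 163 it would be 204.

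**2. Cluster size.** 320 recruited / 16 teams = 20 per team; 256 analysed / 16 = 16 per team. Neither is 38. At 16 per team and the same ICC, DE = 1 + 15 × 0.013 = 1.195.

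**3. Power of 128 per arm, two-sided.** Non-centrality = d × √(n / (2 × DE)):

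- DE 1.5: 0.38 × √(128 / 3.0) = 2.48
- DE 1.195: 0.38 × √(128 / 2.39) = 2.78

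Power = P(|T| > critical value), first with normal quantiles, then with the non-central t on 16 − 2 = 14 df, then on 12 df (two more lost to the organisation strata):

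| DE | alpha | normal | 14 df | 12 df |
|---|---|---|---|---|
| 1.5 | 0.05 | 0.699 | 0.637 | 0.626 |
| 1.5 | 0.05/3 | 0.535 | 0.435 | 0.419 |
| 1.5 | 0.05/4 | 0.494 | 0.386 | 0.370 |
| 1.195 | 0.05 | 0.794 | 0.735 | 0.724 |
| 1.195 | 0.05/3 | 0.651 | 0.541 | 0.522 |
| 1.195 | 0.05/4 | 0.611 | 0.490 | 0.470 |

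**4. Splitting the shortfall at DE 1.5, alpha 0.05.** From 0.80 to 0.70 is about 10 points, from using a one-sided sample size for a two-sided test. From 0.699 to 0.637 is a further 6 points, from the few teams. The total is about 16 points.

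**5. The few-teams component alone.** A design with exactly 0.80 by normal quantiles has 0.741 on 14 df and 0.730 on 12 df. The loss is therefore about 6 or 7 points at alpha 0.05. On 14 df it is 10 to 12 points at 0.05/3 and 0.05/4.

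**6. Check by simulation.** With 8 + 8 balanced teams of 16, ICC 0.013, d = 0.38 and 100,000 runs, power was 0.736 for a t test on team means. It was 0.730 for a variance-component test that pools when the team variance is estimated at zero, which happened in 36 % of runs. The loss is not an artefact of one formula.

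**The case against.** **Multiplying by a design effect is a common planning approximation.** The protocol states no degrees of freedom, so omitting a small-cluster refinement contradicts no sentence in it. That is true of the df component taken alone. It does not rescue the stated 0.80, which already fails under normal quantiles at the stated design effect.

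**The sidedness and cluster-size problems are the larger or plainer ones.** For sidedness at DE 1.5 this is right: about 10 of the 16 points come from there. The df component is still worth correcting in the same recalculation. At 16 per team, two-sided power by normal quantiles is 0.79, so a corrected cluster size would seem to restore the stated power while 14 df gives 0.735.

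**The real analysis may do better.** It is longitudinal with a baseline measurement. If the variance is multiplied by (1 − r²), power on 14 df at DE 1.195 becomes 0.77, 0.80 and 0.85 for r = 0.3, 0.4 and 0.5. At DE 1.5 it is 0.68, 0.71 and 0.76, reaching 0.82 at r = 0.6. This limits what can be said about the power the trial will achieve. But the protocol gives no such correlation and its stated calculation does not mention one. Unequal team sizes would work in the other direction.

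**The loss may be smaller.** If the team variance is estimated near zero, Satterthwaite df can exceed 14. This holds for an individual data set, though the simulation showed no recovery on average.

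**The choice of df method is analysis-plan detail.** This stands. A reader might infer that the protocol plans to test the arm effect against a normal reference. It does not say so; it names a mixed model with a random team intercept and leaves the reference distribution open. That is no finding here.

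**Conclusion.** The point holds as a fault in the stated power. For 128 analysed clients per arm, d = 0.38 and a two-sided 5 % test, the protocol's own design effect gives about 0.70 by normal quantiles and 0.64 on 14 df. With the cluster size implied by the recruitment figures, it gives 0.79 and 0.735.

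Two stronger readings should be resisted.

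- A reader might infer that 6 points is the whole overstatement, or its ceiling. It is neither. It is the few-teams component at alpha 0.05 on 14 df, and the total on the stated inputs is about 16 points. Fitting the strata or testing at the Bonferroni levels enlarges the component. The mismatch between a power stated at 0.05 and tests at 0.05/3 or 0.05/4 exists whatever the df.
- A reader might infer that the trial will have only 64 % power, or that it needs more teams. The documents do not support that: the figure rests on equal team sizes and an unadjusted single comparison, and the gain from the planned longitudinal model cannot be quantified from what is given.

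The normal-approximation origin of 128 is an inference, though the agreement of 128.4 with 128 is close.

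**What to change.** Restate the power for the planned 128 analysed clients per arm in 16 teams, from a two-sided non-central t calculation with 14 df, or 12 if organisation is in the model. Use a design effect that matches the expected number of analysed clients per team, and reconcile 38 with the 16 to 20 per team that the recruitment figures imply. Give the result at the alpha at which the outcome will be tested. If credit is taken for baseline adjustment, state the assumed correlation and its source.

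The cost is one recalculated figure and a sentence of explanation. It requires no extra teams or clients. The drawback is a less favourable stated power, unless a justified baseline correlation offsets it.

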### Statistical analysis

Data will be analysed according to intention-to-treat, meaning that participants will be analysed in the group to which they were allocated by randomization [65]. SPSS 19 will be used for the analysis. Because the study has a cluster randomized design, longitudinal multilevel analysis (linear mixed modeling with random intercepts at both team level and individual level) is the analysis method of choice. First, effectiveness of the CARe Methodology on the three primary outcomes, recovery, social functioning and quality of life, will be evaluated. Subsequently, the effectiveness on four secondary outcomes, hope, empowerment, self-efficacy beliefs and need for care will be evaluated. An alpha correction (i.e., Bonferroni adjustment) will be applied across analysis of the primary measures in order to maintain a family-wise alpha level of 0.05. A separate Bonferroni adjustment will be applied to the set of analysis for the secondary measures to maintain their family-wise alpha level at 0.05. Furthermore, in separate analyses we will assess whether different types of predictors explain the outcomes: (1) client characteristics (age, gender, having a partner, type of housing, diagnosis), (2) symptom severity (BSI), (3) health and day care utilization. Only predictors that influence the prediction of the outcome measures will be added tot the final model. Outcomes will be measured at 10 months and 20 months post-baseline (time will be analyzed as a categorical variable).

To detect significant differences in the baseline characteristics between the intervention group and control group descriptive analysis will be used. When necessary these differences will be taken into account in the analysis. Missing data and drop-outs will be analysed and accounted for by multiple imputation if the assumption of data missing at random (MAR) is not violated [66].

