### Study design

This study is a two-armed cluster RCT that will be executed in teams selected from three organizations for sheltered housing in the Netherlands. These teams all provide sheltered housing and/or supported independent living services. Randomization will be applied at team level and will be stratified by organization. The professionals of the teams in the intervention group will receive a basic training in CARe methodology (three full-day meetings and four half-day meetings; see ‘Intervention’ for further information) while teams in the control group will continue to offer ‘care as usual’. Cluster randomization is necessary because the intervention is offered at team level; reorganization of this structure (i.e., reassigning clients to other teams in case of individual randomization) would disturb the clients’ living situations and relations of trust with their personal key workers, and would therefore be ethically undesirable. Furthermore, cluster randomization reduces contamination between the trial arms as much as possible. However, we will not be able to prevent staff changes completely; therefore we shall monitor this and take this into account in the analysis (see paragraphs outcome measures and statistical analysis). The participating teams will be randomized on an equal basis so an equal amount of teams and clients can participate in both arms. An independent researcher of the Department of Methodology and Statistics of Tilburg University will perform the randomization. The professionals and researchers will be aware of the allocation to the conditions; clients cannot be blinded but it will not be pointed out to them explicitly which condition they are in. All clients in the participating teams will be asked to participate in the study through an informed consent procedure. Standardized questionnaires will be completed at baseline (T0), and at 10 (T1) and 20 months (T2) post baseline (see Fig. 1). Besides client outcomes, the model fidelity of the CARe methodology will be assessed at T1 and T2.

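### Adjustment depends on a search for baseline imbalance, the role of T0 outcome scores is not fixed, and the randomisation stratum is absent from the stated model

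*Protocol article*

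**What the plan says.** Under Study design, the Protocol article states: "Randomization will be applied at team level and will be stratified by organization". There are three organisations and 16 teams. The same section sets the visits: "Standardized questionnaires will be completed at baseline (T0), and at 10 (T1) and 20 months (T2) post baseline". Table 1 lists every primary and secondary outcome at all three.

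The Statistical analysis section names the model as longitudinal, with "linear mixed modeling with random intercepts at both team level and individual level", and adds that "time will be analyzed as a categorical variable". The sentence that contains this remark mentions only the 10- and 20-month measurements. Nowhere does the section say whether the T0 score of an outcome is a response, a covariate or unused.

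Two rules govern covariates:
- For candidate predictors ("client characteristics (age, gender, having a partner, type of housing, diagnosis"; also symptom severity and care utilisation): "Only predictors that influence the prediction of the outcome measures will be added". Organisation is not among them.
- For imbalance: "To detect significant differences in the baseline characteristics between the intervention group and control group descriptive analysis will be used", followed by "When necessary these differences will be taken into account in the analysis".

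**The concern.** Three features of the stated model work against a trial with only eight teams per arm.

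- **Imbalance rule.** Teams are randomised, so a significant baseline difference shows a chance event. It does not show which covariates predict the outcome. Adjustment triggered this way makes the primary model depend on the data and may leave out the covariates that matter most. The second rule, on predictors, adds to this.
- **Role of T0 scores.** An outcome's own baseline is usually its best predictor and is already collected. Leaving its use open leaves open both the precision and the definition of the treatment contrast (level at follow-up, or change from T0).
- **Team-level terms.** The stratum is not named in the model, so balance achieved by stratification may go uncredited. If the effect is a change from T0, a team intercept that is constant over time drops out of it, and any differing team trajectories are missing from its standard error. Such differences are plausible: training and coaching act on teams, fidelity is audited team by team, and the Study design section expects staff changes.

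**Working it through.** **Inputs from the Protocol article.** Power section: d = 0.38, two-sided alpha 0.05, design effect (DE) 1.5 from cluster size 38 and ICC 0.013, 128 per condition, 160 recruited, 16 teams. Statistical analysis: Bonferroni over three primary outcomes, so 0.05/3 = 0.0167 (z = 2.394). Completers per team: 128/8 = 16.

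**Assumptions, not in the document.** Correlation r between T0 and follow-up of 0.5 to 0.7. Team autocorrelation (the share of team variance that is constant over time) of 0.8 to 0.5. The effect size 0.38 is the plan's figure for empowerment, a secondary outcome. It is used for the primary family only because the plan gives no other.

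**The plan's own figures.** DE = 1 + 37 × 0.013 = 1.481, stated as 1.5; 128/0.8 = 160. Both agree. The 128 does not follow from a two-sided 5% test (108.7 × 1.5 = 163); it matches a one-sided one (85.6 × 1.5 = 128.4). That is a separate matter, and 128 is taken as given here.

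**Step 1: power by use of T0.** Effective n per arm = 128/1.5 = 85.3. Power = Φ(0.38 × √(85.3/(2v)) − 2.394), where v is the variance relative to a follow-up-only comparison: 1 if T0 is unused, 2(1 − r) for change from T0, and 1 − r² with T0 as a covariate. DE is held at 1.5 throughout.

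| Analysis | v at r = 0.5 | Power | v at r = 0.7 | Power |
|---|---|---|---|---|
| T0 unused | 1.00 | 0.54 | 1.00 | 0.54 |
| T0 as response (change) | 1.00 | 0.54 | 0.60 | 0.79 |
| T0 as covariate | 0.75 | 0.68 | 0.51 | 0.86 |

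Covariate adjustment has 0.75 of the change contrast's variance at r = 0.5 and 0.51/0.60 = 0.85 at r = 0.7.

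**Step 2: error of the change contrast if T0 is a response.** In a balanced design, true variance divided by model variance = 1 + (m − 1)ρ. Here ρ = team-by-time variance / (team-by-time + residual variance), with total variance 1, team-by-time variance 0.013 × (1 − autocorrelation) and residual variance 0.987 × (1 − r).

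Example, autocorrelation 0.5, r = 0.5, m = 16: ρ = 0.0065/(0.0065 + 0.4935) = 0.013; ratio = 1 + 15 × 0.013 = 1.195; type I error = 2[1 − Φ(1.96/√1.195)] = 0.073.

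| Team autocorrelation | Variance ratio (r = 0.5 to 0.7) | Type I at nominal 0.05 | At nominal 0.0167 |
|---|---|---|---|
| 1 | 1.00 | 0.050 | 0.0167 |
| 0.8 | 1.08 to 1.13 | 0.059 to 0.065 | 0.021 to 0.024 |
| 0.5 | 1.20 to 1.32 | 0.073 to 0.088 | 0.029 to 0.037 |

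A simulation of 8,000 trials per case (r = 0.6, eight teams per arm, 16 clients per team, three visits) gave 0.049, 0.059 and 0.075 for autocorrelation 1, 0.8 and 0.5. A t-test on team-mean change in the same data gave 0.047 to 0.050.

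Step 1 uses the plan's DE, which rests on 38 per team; step 2 uses the 16 completers per team implied by 128 per condition. With 16 per team, DE is 1 + 15 × 0.013 = 1.195 and power with T0 unused is 0.65 rather than 0.54.

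**Step 3: stratum.** No size can be given, because the document states no between-organisation variance.

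**The case against.** A journal article condenses a fuller plan. A short parenthesis on random intercepts need not list every fixed effect, and organisation is not excluded. This stands in part: the missing stratum is the weakest element and would not carry the point alone. It does not reach the imbalance rule or the random structure, which the article states outright.

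Four stronger readings are tempting, and the document does not support them.

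- *Outcome scores at T0 are used only after an imbalance search.* The rule concerns baseline characteristics. In a model described as longitudinal, T0 scores may already be responses. The defect is that the text leaves this open.
- *The plan both wastes baseline information and understates the error of change.* The full loss, 0.54 against 0.68 to 0.86, needs T0 to be unused. The error inflation needs T0 to be a response. They cannot both apply.
- *P-values for change will be too small.* That holds only if teams differ in their change over time. The document gives no team-by-time variance, and with constant team effects the error is 5%.
- *Omitting organisation adds to the same bias.* Omitting a stratum usually makes standard errors too large, the opposite direction, and a constant organisation effect cancels from a change contrast.

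It is also fair to say that the proposed model is one of several acceptable ones. What matters is that one is fixed in advance without an imbalance test.

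**Conclusion.** The point holds in this limited form, and the plan should be changed. The imbalance rule is unsound under either reading. The open role of T0 is a defect because it decides which cost applies: a power shortfall of 0.14 to 0.32 (0.54 against 0.68 to 0.86) if T0 is ignored; or, if T0 is a response, a shortfall of 0.14 at r = 0.5 or 0.07 at r = 0.7, together with a possible type I error of about 6 to 9% at nominal 5%. At the Bonferroni level the corresponding error is about 2.1 to 3.7% against 1.67%, so the intended family-wise protection would not be assured.

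These sizes rest on the assumed correlations and team autocorrelations. At the plan's ICC of 0.013 the inflation is modest to moderate, and it vanishes if team effects do not vary over time. The stratum omission is real in the text but has no computable size.

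**What to change.** Replace the two data-driven covariate rules for the primary analysis with one fixed model, the same for every outcome:

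- Responses: T1 and T2.
- Fixed effects: arm, time, arm-by-time, organisation, and the T0 value of the same outcome.
- Random effects: client, team and team-by-time, with small-sample degrees of freedom (for example Satterthwaite).
- Baseline table: descriptive only, with no search for significant differences and no adjustment triggered by it.
- Predictor analyses: kept as separate, exploratory analyses.

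This changes analysis wording and needs no new data. Organisation uses 2 of about 14 team-level degrees of freedom (16 teams less 2 arms). The team-by-time variance may be estimated at zero with so few teams, so the plan should say in advance what is done in that case.

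### A client random intercept alone ties T0, T1 and T2 to one variance and one correlation; if the T0–T2 correlation is the weaker one, the 20-month standard error is too small

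*Protocol article*

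**What the plan says.** The Study design section sets three waves: "Standardized questionnaires will be completed at baseline (T0), and at 10 (T1) and 20 months (T2) post baseline". The Statistical analysis section of the same article names the model as "linear mixed modeling with random intercepts at both team level and individual level" and adds that "time will be analyzed as a categorical variable". The software is fixed: "SPSS 19 will be used for the analysis".

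The section names no residual covariance structure and no random slope. It gives no within-client correlation and no variance by wave. It also leaves open whether T0 is part of the response or a covariate; the sentence on timing mentions only the follow-up waves: "Outcomes will be measured at 10 months and 20 months post-baseline".

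On multiplicity: "An alpha correction (i.e., Bonferroni adjustment) will be applied across analysis of the primary measures". With three primary outcomes, each is tested at 0.05/3 = 0.0167.

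**The concern.** In a random-intercept model with independent residuals of one variance, the intercepts carry all the dependence between a client's scores. The model then has a single variance at every wave and a single correlation for every pair of waves. The change from T0 to T1 and the change from T0 to T2 therefore get the same standard error, although one spans 10 months and the other 20.

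If scores 20 months apart are less alike than scores 10 months apart, the model uses an averaged correlation where a lower one applies. The 20-month effect is then tested above its Bonferroni level and its confidence interval is too narrow. All three primary and four secondary outcomes use the same model, so the same assumption runs through all of them.

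**Working it through.** **Inputs.** From the article: three waves; client and team random intercepts; 0.0167 per primary outcome (two-sided critical value z = 2.394); 16 teams; 160 clients recruited per group, hence 320. The article has no figure of its own to reproduce on this point. The correlations below, written r01/r12/r02 for T0–T1, T1–T2 and T0–T2, are assumptions chosen to show a range. Variances are set to 1 unless stated.

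**Formula, T0 in the response.** With balanced data the residual variance of the random-intercept model converges to 1 − r̄, where r̄ is the mean of the three correlations. The model gives each change the variance 2(1 − r̄). The true variance is 2(1 − r01) for T1 and 2(1 − r02) for T2. A team intercept that is constant over time cancels from a change. Hence

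- SE ratio (model/true) at T2 = √[(1 − r̄)/(1 − r02)]
- SE ratio at T1 = √[(1 − r̄)/(1 − r01)]
- actual error rate = 2Φ(−2.394 × ratio)

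The T2 ratio is below 1 exactly when r̄ > r02, that is, when r02 < (r01 + r12)/2.

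Example, 0.7/0.7/0.5: r̄ = 0.633; T2 ratio = √(0.367/0.5) = 0.856; error rate 2Φ(−2.050) = 0.040.

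**Formula, T0 as covariate.** The residual variances are v1 = 1 − r01² and v2 = 1 − r02², and the model pools them. The T2 ratio is √[((v1 + v2)/2)/v2]. For the same example v1 = 0.51, v2 = 0.75, pooled 0.63; ratio √(0.63/0.75) = 0.917; error rate 0.028.

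**Joint 2-df test.** The model's Wald statistic is a weighted sum of two chi-squares; its large-sample rejection rate at nominal 0.0167 is in the last column.

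| r01/r12/r02 | T1 ratio | T2 ratio | T2 error rate | T2 ratio, T0 covariate | error rate | joint test |
|---|---|---|---|---|---|---|
| 0.60/0.60/0.60 | 1.00 | 1.00 | 0.017 | 1.00 | 0.017 | 0.017 |
| 0.65/0.65/0.60 | 1.02 | 0.957 | 0.022 | 0.975 | 0.020 | 0.017 |
| 0.60/0.60/0.45 | 1.06 | 0.905 | 0.030 | 0.949 | 0.023 | 0.018 |
| 0.70/0.70/0.50 | 1.11 | 0.856 | 0.040 | 0.917 | 0.028 | 0.021 |
| 0.80/0.80/0.64 | 1.13 | 0.839 | 0.045 | 0.897 | 0.032 | 0.023 |
| 0.50/0.75/0.50 | 0.91 | 0.913 | 0.029 | 1.00 | 0.017 | 0.022 |

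The last row has the two follow-ups closer to each other than to baseline. Both standard errors are then about 9% too small when T0 is in the response, so the 10-month error runs the other way from the decay rows. Unequal variances matter less at T2: at a common correlation of 0.6 with SDs rising 1, 1.1, 1.2 the T2 ratio is 0.99 and the T1 ratio 1.05.

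**Simulation check** (8 teams of 16 clients per arm, ICC 0.013, 4,000 replicates). Under 0.7/0.7/0.49 the T2 rejection rate was 0.093 at nominal 0.05 and 0.044 at 0.0167 (closed form 0.095 and 0.041). Under equal correlations of 0.6, rejection at nominal 0.05 was 0.049 at T1 and 0.048 at T2. In a separate run of 20,000 replicates at nominal 0.0167, the sets 0.6/0.6/0.45 and 0.7/0.7/0.5 gave 0.031 and 0.040 with the random intercept, against 0.017 to 0.018 with an unstructured covariance.

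**The case against.** The strongest reply is that the article fixes the random effects but not the residual matrix. A mixed model can combine random intercepts with a structured or heteroscedastic residual, and an article often leaves that to the analysis plan. This stands in part: equal residual variance is the ordinary reading, not a statement in the text. Against it, an unstructured residual matrix would make the client intercept redundant, so naming that intercept suggests that it is meant to carry the repeated measures.

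Second, a reader might infer that the 20-month standard error will be too small and the 10-month one too large. The article does not support this as a fact. It gives no correlations; equal correlations and variances produce no error, and the 10-month direction reverses in the last row of the table. In a population with long-term illness in sheltered or supported housing, stable differences between clients are plausible, and decay may be mild.

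Third, a reader might infer that every primary test exceeds its Bonferroni level by the full amount. The article does not say that the T0–T2 contrast is the test. Under a joint group-by-time test the errors at the two waves largely offset. If T0 is a covariate, only two response waves remain, so equal correlation imposes nothing and only equal variance does. Both replies stand, and they shrink the size.

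**Conclusion.** The point holds conditionally. The stated model, as ordinarily fitted, imposes equal variance and equal correlation across the waves without justification. When r02 is below the average of the other two correlations (equal variances assumed), the single 20-month contrast has a standard error about 4% too small under mild decay and 10 to 16% under marked decay, which turns 0.0167 into 0.022 to 0.045. With T0 as covariate, the same decay patterns give about 2 to 10% (0.020 to 0.032); for the joint test the rate is about 0.017 to 0.023.

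These figures rest on assumed correlations, balanced data and large-sample approximations, and they leave out any team-by-time variation, which is a separate matter. It is a robustness improvement worth making, not an error shown to be present.

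**What to change.** In the Statistical analysis section, replace the individual-level random intercept with an unstructured within-client covariance over the response waves, fitted in SPSS MIXED through a REPEATED statement by client, and keep the team-level random effects. Name a heterogeneous first-order autoregressive structure as the fallback if the model does not converge. The unstructured form covers every within-client pattern in the table, including equal correlations, so the choice need not wait for knowledge of the true correlations.

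Cost: one sentence. With three response waves, six within-client parameters replace two (four more), estimated on some 320 recruited clients; with T0 as covariate, three replace two. The 20-month confidence interval may be somewhat wider.
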